## Methods

### Participants

#### Overview

All Norwegian residents have a unique personal identification number, which is used in health and administrative national registries and can be used to merge data across different registries. In this study, we identify all eligible individuals based on information available from the National Population Register and the Norwegian Immunisation Registry SYSVAK.

The trial has 3 separate populations of individuals who are aged 65 years or older and who reside in Norway, namely (1) the entire Norwegian population (except immigrants born in Poland or Ukraine); (2) immigrants born in Poland; and (3) immigrants born in Ukraine.

#### Inclusion Criteria

Aged 65 years and older (age at the end of 2025, ie, born in 1960 or earlier).Resident in Norway and have a valid ID number on September 1, 2025.Have a smartphone number in the common contact register.

#### Exclusion Criteria

Have received the 2025 influenza vaccine prior to the SMS nudge dispatch date.Have emigrated or died before SMS nudge dispatch date.

### Interventions

Participants in the intervention arms receive an SMS reminder for influenza vaccination in Norwegian, Polish, or Ukrainian. Participants in the control arm do not receive an SMS reminder for influenza vaccination, which is “standard care” in Norway. A description and overview of the InfluSMS study arms and participant flow are shown in Table 2 and Figure 1.

**Table 2 table2:** InfluSMS study arms.

Study arm	Description	Population
Control	Standard care: Individuals do not receive an SMS reminder for influenza vaccination.	General population Immigrants born in Poland Immigrants born in Ukraine
Intervention 1	Norwegian nudge: Individuals receive an SMS in Norwegian language at the start of the influenza season; to remind them they are recommended to get the influenza vaccine	General population Immigrants born in Poland Immigrants born in Ukraine
Intervention 2	Polish or Ukrainian nudge: Individuals receive an SMS in the official language of their native country (ie, Polish or Ukrainian) at the start of the influenza season, to remind them they are recommended to get the influenza vaccine	Immigrants born in Poland Immigrants born in Ukraine

**Figure 1 figure1:**
[figure not shown]
InfluSMS participant flowchart.

### Outcomes

The primary outcome measure is having been vaccinated against influenza during the 3 months following the SMS dispatch date in the 2025-2026 influenza season (yes or no, for each individual), as registered in the Norwegian Immunisation Registry SYSVAK [31]. Notification of influenza vaccination to SYSVAK is obligatory for vaccine administrators and does not require patient consent. Follow-up during this trial is passive and does not require any effort from the participants.

Effects will be assessed by influenza vaccination coverage, that is, percent uptake, which will be compared between strategies. SMS nudging will take place at the earliest timepoint at which vaccines for the upcoming influenza season become widely available across the country, which usually is around week 42. All SMS nudges will be dispatched within 1 week. Each individual will be followed up through SYSVAK for 3 months after their SMS dispatch date. We end follow-up at 3 months because we expect that the potential effect of an SMS nudge will be exhausted by then, and because most vaccinations in the influenza vaccination program will have occurred by the end of this period.

Time to influenza vaccination, that is, the number of days elapsed between the SMS dispatch date and the influenza vaccination date (as registered in SYSVAK), is a secondary outcome measure.

We will also address coverage of COVID-19 vaccination as an outcome in the exploratory analyses.

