### Sample Size

#### Primary Objective 1: General Population in Norway

We will identify all individuals in the National Population Register that fulfill the eligibility criteria, and among those, make a random selection to receive the Norwegian nudge (intervention 1). We power for a 1% point minimal detectable increase in uptake in the SMS arm compared to the control arm in the general population because the intervention is relatively inexpensive and might be cost-effective even with low effectiveness on coverage. To achieve this minimal detectable increase with a baseline uptake rate of 60%, a power of 0.8, and a 1-sided α of .05, we need to randomize 18,788 individuals to intervention 1. However, based on available statistics, some 20% of individuals may have received the influenza vaccine before the scheduled trial start date and will be excluded from the trial after randomization. We thus need to randomly sample at least 23,485 individuals aged 65 years or older from the entire Norwegian population (except those born in Poland or Ukraine) to be allocated to intervention 1 to be able to detect an increase of 1 percentage point (23,485×80/100=18,788). The control group will be the rest of the Norwegian population that fulfills the eligibility criteria. Currently, there are circa 1.1 million persons aged 65 years or older who reside in Norway. We use this large group as a control because it gives the study high power, the inclusion of individuals receiving standard care carries no cost, and it will provide real-world data on the entire older adult population in Norway.

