**SYSVAK**		
	National ID	Used to identify eligible individuals and link to study ID. Not shared with InfluSMS project group
	Date of vaccination	Determine if date of vaccine was before/after nudge, and impact of vaccination
	Disease against which the vaccine protects: Influenza COVID-19	Determine who received each vaccine, to calculate vaccination coverages

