### Statistical Methods

All individuals randomized will be analyzed, except individuals who die or emigrate during follow-up, who will be excluded from the analyses. We expect exclusions to be evenly distributed between treatment arms due to the randomized design. Additionally, we anticipate a low proportion of excluded individuals given the relatively short follow-up time of the trial. According to official statistics [33], we can expect approximately 2800 deaths and 100 emigrations per month among the nearly 1.1 million persons aged 65 years or older residing in Norway, which accounts for 0.3% of this population.

As recommended for binary RCT outcomes [34], coverage differences between treatment arms will be expressed on absolute and relative scales, that is, as percentage point differences and as relative risks, with associated 95% Wald CIs. The primary focus will be on absolute scale analyses because they may be most informative for public health decision-making. Absolute estimates will be derived from linear regressions [35], while relative estimates will be derived from generalized linear models with a log-binomial link function [36]. Overall interactions (specifically secondary objectives 1 and 2, where differences between treatment arms will be compared between country backgrounds) will be assessed by likelihood ratio tests and, if significant, further analyzed by the participation differences between factor levels of the variables that interact.

We will compare the time to vaccination (ie, the number of days elapsed between the SMS dispatch date and the influenza vaccination date) between trial arms by the Kaplan-Meier method and the log-rank test.

We assume the registry data for randomized individuals to be close to complete and thus will not impute missing values.

As sensitivity analyses, we will exclude households consisting of at least two or more people aged 65 or older. Comparing the results of these analyses with the main results will indicate whether there may be spillover effects of the SMS interventions within households. Moreover, it will exclude persons living in nursing homes, who may experience easier access and less autonomy regarding influenza vaccination. In exploratory analyses, we will also address the potential effects of SMS nudging for influenza vaccination on the coverage of COVID-19 vaccination. We will use the same statistical methods for these sensitivity and exploratory analyses as described for the main analyses.

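### Exclusion, outcome window and time to vaccination run from an SMS dispatch date that controls do not have; unless one date is fixed for all arms, the SMS-control comparison can be biased by about the 1-point target

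*Protocol article*

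**What the plan says.** Three definitions in the protocol article hang on the dispatch date.

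- Exclusion Criteria: "Have received the 2025 influenza vaccine prior to the SMS nudge dispatch date". Death or emigration before that date also excludes.
- Outcomes, primary measure: vaccination within 3 months of dispatch. The date is personal: "Each individual will be followed up through SYSVAK for 3 months after their SMS dispatch date". It may also vary between people: "All SMS nudges will be dispatched within 1 week".
- Outcomes, secondary measure: days from dispatch to vaccination.

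Controls receive no SMS (Interventions, Table 2). Table 3 lists the date on which the SMS was sent but no index date for people without one, and the key file under Data Collection holds arm and exclusion status but no date. Table 3 gives the purpose of the SYSVAK vaccination date as: "Determine if date of vaccine was before/after nudge, and impact of vaccination".

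On sequence, Primary Objective 1 has about 20% of people already vaccinated and removed after randomisation, while Assignment of Interventions places randomisation after exclusions have been assessed.

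Statistical Methods analyses everyone randomised "except individuals who die or emigrate during follow-up, who will be excluded from the analyses".

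**The concern.** As written, the eligibility rule and primary outcome cannot be applied to controls, who are about 98% of the general population (23,485 of 1.1 million is 2.1%) and one third of each immigrant group. Someone has to choose a control date later.

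Suppose controls get the first day of dispatch and SMS recipients their own day. An SMS-arm member vaccinated on day 2 and due a message on day 4 is then excluded. The identical control counts as a success. This removes likely vaccinees from one arm only, in a week when vaccine has just become widely available. The Kaplan-Meier time axis has the same mismatch. Objective 1 is the most exposed because its target is small: "We power for a 1% point minimal detectable increase in uptake in the SMS arm compared to the control arm". A very large control group adds precision but does not remove bias.

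**Working it through.** **Plan's own figures.** The article states: "with a baseline uptake rate of 60%, a power of 0.8, and a 1-sided α of .05, we need to randomize 18,788 individuals". The inflation reproduces exactly: 18,788 / 0.80 = 23,485. The 18,788 itself is close to a two-sided α of .05 with the rest of 1.1 million as controls (19,119); the stated 1-sided α gives 14,999. That is a separate matter and does not affect what follows.

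**Inputs from the article.** Season coverage is 64.4% (all), 19.0% (Poland) and 3.1% (Ukraine), from Table 1. Vaccinated before dispatch: 20%, 6% and 1% (Sample Size). Dispatch takes up to 1 week and follow-up is 3 months, taken as 13 weeks.

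**Assumptions, not in the article.** No true effect. Uptake is even over the 13 weeks and season coverage is reached by their end. Dispatch is spread evenly over the week, giving a mean offset of 3 to 3.5 days. The control clock starts on the first day.

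**Formula.** Let p be coverage among those eligible on day 0, and f the fraction vaccinated between day 0 and their own message.

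- Control arm: p
- SMS arm: (p - f)/(1 - f)
- Shift: (p - f)/(1 - f) - p = -f(1 - p)/(1 - f)

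**General population.** p = (64.4 - 20)/80 = 0.555, or 0.555/13 = 4.27% per week.

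- Offset 3 days: f = 0.0427 × 3/7 = 0.0183; shift = -0.0183 × 0.445/0.9817 = -0.83 points.
- Offset 3.5 days: f = 0.0213; shift = -0.0213 × 0.445/0.9787 = -0.97 points.

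**Poles.** p = (19.0 - 6)/94 = 0.138; f = 0.0046 to 0.0053; shift -0.4 to -0.5 points, against a 4-point detectable difference.

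**Ukrainians.** p = (3.1 - 1)/99 = 0.021; f = 0.0007 to 0.0008; shift about -0.1 point, against 2 points.

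**Sensitivity, general population.**

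- *Launch-week uptake twice the average:* f = 0.0366 to 0.0427; shift -1.7 to -2.0 points.
- *Front-loaded uptake* (exponential, mean 42 to 21 days): -1.5 to -3.4 points, dispatch on days 0 to 6.
- *Control clock on day 6:* controls fall by 0.0366 × 0.445/0.9634 = 1.69 points and the SMS arm by 0.83, so the difference is +0.86. The sign reverses.
- *Vaccinations gained after day 91:* the even-uptake case allows none. A gain g changes the SMS arm to (p - f + g)/(1 - f), so the shift vanishes if g = f(1 - p) = 0.445f, that is, if late uptake still ran at about 45% of the dispatch-week rate. Outcomes expects most vaccinations to be over by then. The front-loaded results already include late gains.
- *Same date for all arms:* f is equal in every arm and the shift is 0.

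**Deaths and emigrations.** 2,900 per month / 1.1 million = 0.26%, the article's 0.3%. Over 3 months: 8,700 / 1.1 million = 0.79%.

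**The case against.** The strongest reply is that one common date is a natural reading. The sample-size sections speak of a scheduled start or dispatch date in the singular, and the key file gives everyone, controls included, an exclusion status, which presupposes some reference date. An analysis plan not shown could fix it. This stands to the extent that the bias is conditional and is zero if that date is used throughout. But no sentence applies it to controls, and the outcome definition points to a personal date instead.

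Second, Assignment of Interventions puts exclusion before randomisation, so exclusion could not differ by arm. A reader might infer from the exclusion rule that differential selection after randomisation is built into the design; the article does not support that, because its two statements on sequence conflict. Even so, messages go out after allocation, so anyone vaccinated between allocation and their own message meets the exclusion criterion only afterwards, and the outcome window and Kaplan-Meier origin remain undefined for controls.

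Third, size and sign rest on unstated choices. This is correct: the article gives only an upper limit on dispatch time and no daily uptake. A reader might also arrive at about -1.8 points under even uptake by moving only the outcome window. That would keep people vaccinated before their message and score them as unvaccinated, which the exclusion criterion rules out.

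Fourth, a reader might infer that every comparison is compromised. Objective 4 compares two SMS arms that both have dispatch dates, and the effect on the immigrant comparisons with control is small.

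Fifth, removing deaths and emigrations after time zero might be read as a further bias. The article expects balance between arms, and nothing here shows otherwise. Nor does it say that vaccination after emigration reaches SYSVAK, so outcome status cannot be taken as known for emigrants.

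**Conclusion.** The point holds as a conditional one. The article fixes time zero in a form that cannot be applied alike to SMS and control arms. The consequence could be as large as the effect objective 1 is designed to detect: about -0.8 to -1.0 point under even uptake, evenly spread dispatch and a first-day control clock. A bias is not demonstrated, because a single date for everyone removes it. What makes the point matter is that the choice of control date can set both the size and the sign of the shift, and that choice is left open. The main exposure is objective 1 and, in the same way, the SMS-control time-to-vaccination comparisons.

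**What to change.** Define one calendar index date, the first day of dispatch, for every person in every arm. Use it for the already-vaccinated, dead or emigrated exclusions, for the 3-month outcome window and for the Kaplan-Meier origin. Alternatively, assign a dispatch day to everyone, controls included, before allocation and use that day as time zero. Reconcile Primary Objective 1 with Assignment of Interventions on whether exclusion precedes randomisation.

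The cost is protocol wording and one derived date in the key file; 18,788 and 23,485 are unchanged. With the common date, some SMS-arm members will be vaccinated before their message and count as intervention events: about 2%, or 18,788 × 0.0183 to 0.0213, roughly 340 to 400 people under the assumptions above. The dilution is slight, about 0.02 of a 1-point effect (1 × 0.02). The assigned-day option avoids this but requires a stored date for every control.

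Minor and separate: describe the 0.3% for deaths and emigrations as a one-month figure, about 0.8% over follow-up. Keeping deaths in the coverage analysis and censoring them in the Kaplan-Meier analysis is a simple option, not a correction of a shown bias.

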**Table 1 table1:** Nationwide coverage^a^ of influenza and COVID-19 vaccine among individuals aged 65 years or older^b^ during the 2023-2024 influenza season in Norway, stratified by country background^c^.

	Total population	Influenza vaccine^d^ , n (%)	COVID-19 vaccine^e^, n (%)
All	1,020,728	656,990 (64.4)	555,745 (54.4)
Born in Norway	941,657	623,598 (66.2)	530,923 (56.4)
Born in Sweden	7129	4520 (63.4)	3976 (55.8)
Born in Denmark	5966	3820 (64.0)	3372 (56.5)
Born in United Kingdom	4606	2888 (62.7)	2594 (56.3)
Born in Germany	3991	2000 (50.1)	1783 (44.7)
Born in Poland	3888	740 (19.0)	520 (13.4)
Born in Ukraine	3843	119 (3.1)	72 (1.9)

^a^Norwegian Immunisation Registry SYSVAK [31] data, extracted May 31, 2024.

^b^Age on December 31, 2023 (born 1958 or earlier).

^c^The most common country backgrounds among individuals aged 65 years or older.

^d^Received at least 1 dose of influenza vaccine between September 1, 2023, and May 29, 2024.

^e^Received at least 1 dose of COVID-19 vaccine between September 1, 2023, and May 29, 2024.

Poles and Ukrainians in Norway also had a very low uptake of the COVID-19 vaccine, both during [32] and after (Table 1) the pandemic, showing that low uptake of adult vaccines in these populations is not limited to influenza vaccination. Thus, interventions that may overcome vaccine hesitancy, which is prominent in Ukraine and Poland [15,16], as well as potential access barriers such as language, are likely to have a general relevance for vaccine uptake.

A recent systematic review highlighted language and tailored text message nudges for improving vaccine uptake as understudied [30]. We are not aware of any studies that have investigated the effectiveness of SMS nudging for influenza vaccination in several languages among immigrant populations.

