### Objectives

The primary objectives of the InfluSMS trial are to establish whether (1) influenza vaccination nudging by SMS in the Norwegian language increases influenza vaccine coverage compared to standard care, among the Norwegian population aged 65 years and older; (2) influenza vaccination nudging by SMS in Polish or Ukrainian language increases influenza vaccine coverage compared to standard care, among older adults of Polish or Ukrainian background, respectively; (3) influenza vaccination nudging by SMS in Norwegian language increases influenza vaccine coverage compared to standard care, among older adults of Polish or Ukrainian background, respectively; and (4) influenza vaccination nudging by SMS in Polish or Ukrainian language increases influenza vaccine coverage more than nudging by SMS in Norwegian language among older adults of Polish or Ukrainian background, respectively.

For primary objectives 1-3, we hypothesize that SMS nudging will increase coverage. If this hypothesis is not confirmed, the interventions investigated here are futile from a public health perspective, and the remaining study objectives will not be investigated. For primary objective 4, we hypothesize that an SMS in the official language of the native country of each immigrant population will be more effective in increasing coverage than an SMS in Norwegian.

The secondary objectives are to establish whether (1) the effect of SMS nudging in the Norwegian language differs by country background; (2) the effect of SMS nudging in the official language of their native country differs between older adults of Polish or Ukrainian background; (3) SMS nudging for influenza vaccination is cost-effective compared to standard care; (4) SMS nudging for influenza vaccination influences coverage of COVID-19 vaccination; and (5) the time to vaccination differs by the comparisons described in the primary objectives.

Secondary objectives 1-4 are exploratory and have no hypotheses. For secondary objective 5, we hypothesize that SMS nudging will shorten the time elapsed to vaccination.

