We will develop a decision analytic model that can evaluate the potential cost-utility of each nudge compared to standard care and each other. The model will be based on coverage differences observed in the trial and will incorporate implications of increased coverage on the spread of influenza and its consequences for the use of health care resources. Data on reduced influenza from increased uptake will be based on effect estimates of vaccination from the best available scientific evidence. Costs associated with the intervention as well as with increased uptake of the vaccine will be recorded in detail during the project phase. Direct medical costs related to the downstream use of health care services will also be incorporated into the model. The cost-utility analysis will be based on Norwegian guidelines [37], conducted according to standard principles for health economic evaluation [38], and reported according to current guidelines [39].

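### Follow-up stops 3 months after the SMS, so vaccinations moved across that line would read as added coverage, and no planned analysis can tell the two apart (mainly objective 1)

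*Protocol article*

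**What the plan says.** Under Outcomes, the primary outcome is "having been vaccinated against influenza during the 3 months following the SMS dispatch date in the 2025-2026 influenza season". Dispatch is planned for when vaccines become widely available, "which usually is around week 42". Two reasons are given for the window. The first is "We end follow-up at 3 months because we expect that the potential effect of an SMS nudge will be exhausted by then". The second is "because most vaccinations in the influenza vaccination program will have occurred by the end of this period". The share of vaccinations that falls later is not stated.

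Under Objectives, secondary objective 5 asks whether "the time to vaccination differs by the comparisons described in the primary objectives", and for it the protocol states "we hypothesize that SMS nudging will shorten the time elapsed to vaccination". Statistical Methods analyses this by Kaplan-Meier and log-rank test.

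For the cost-utility analysis, Statistical Methods says: "The model will be based on coverage differences observed in the trial". Results expects the outcome data in the first quarter of 2026 and publication in the fourth.

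The background figures in Table 1 use a longer window for an earlier season: "Received at least 1 dose of influenza vaccine between September 1, 2023, and May 29, 2024". The sample size section takes its Polish and Ukrainian baselines from that table.

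**The concern.** An arm difference at 3 months has two possible sources. Some people are vaccinated who otherwise would not have been. Others would have been vaccinated after mid-January anyway and are brought into the window. The first is increased coverage; the second is earlier vaccination, and it disappears by season end.

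Exhaustion of the SMS effect does not settle this. It concerns whether the message still prompts people after month 3, not whether controls catch up after month 3. The protocol's own expectation of faster vaccination makes some movement plausible, and the time-to-vaccination analysis covers the same 3 months, so it cannot show whether the arms converge afterwards.

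At stake is what a small positive result means in the general population, where the design target is 1 percentage point. Confirmation of objectives 1 to 3 also decides whether the remaining objectives are pursued, and the observed difference feeds the cost-utility model.

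**Working it through.** **1. Where the window ends.** Week 42 of 2025 is 13-19 October. Three months later is 13-19 January 2026, with up to a week of dispatch spread. From 19 January to 29 May (the closing day used in Table 1) is 130 days.

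**2. The plan's own figure.** The sample size section gives 18,788 in the SMS arm for 60% versus 61%, power 0.8, one-sided alpha .05. With those inputs and a very large control arm, about 14,900 to 15,080 are needed. The stated number comes from a one-sample formula with two-sided alpha: (1.96 × √0.24 + 0.842 × √(0.61 × 0.39))² / 0.01² = 18,788. The inflation is right: 18,788 / 0.8 = 23,485. At 18,788 the one-sided power for 1 point is about 0.87, so the number is conservative. That mismatch is a separate matter; nothing below depends on it.

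**3. Size of a pure timing effect.** Let the true season-end effect be zero. Then

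D = B × L × m

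- D is the apparent 3-month difference in points.
- B is baseline coverage (60%, 19% and 3%, from the sample size section).
- L is the share of vaccinees who would come after the window. This is an assumption; the documents give none.
- m is the fraction of those whom the SMS moves across the line. This is also an assumption.

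Only moves across the 3-month line enter D. A vaccination brought forward within the window leaves the primary outcome unchanged.

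General population, B = 60:

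| L | late vaccinations (points) | D at m = 25% | D at m = 50% |
|---|---|---|---|
| 1% | 0.6 | 0.15 | 0.3 |
| 2% | 1.2 | 0.3 | 0.6 |
| 5% | 3.0 | 0.75 | 1.5 |

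At the top of this grid (L = 5%, m = 50%), Poland gives 19 × 0.05 × 0.5 = 0.475 points against a 4-point detectable increase. Ukraine gives 3 × 0.05 × 0.5 = 0.075 points against 2.

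**4. What it takes to reach each target by timing alone.** L × m must equal target / B:

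- General population: 1/60 = 1.67% of vaccinees, for example 5% late and one third of them moved.
- Poland: 4/19 = 21%.
- Ukraine: 2/3 = 67%, which cannot occur if most vaccinations fall inside the window.

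**5. Chance that a pure timing shift is declared a gain (general population).** Take a total of 1.1 million × 0.9 (with a phone number) × 0.8 (not yet vaccinated) = 792,000, so 773,212 controls. The 0.9 is an assumption, borrowed from the 10% without a number in the immigrant calculation. The standard error is √(0.6 × 0.4 × (1/18,788 + 1/773,212)) = 0.36 points. With one-sided alpha .05 the chance is Φ(D/SE − 1.645):

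- D = 0.25: about 17%
- D = 0.5: about 40%
- D = 0.75: about 67%
- D = 1.0: about 87%

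**6. A lower anchor for m.** The 1-point target is 1/40 = 2.5% of the 40% otherwise unvaccinated. The 6-point mail effect cited from Finland, applied to the same 40%, is 6/40 = 15%. With these as m, D runs from 0.6 × 0.025 = 0.015 to 3.0 × 0.15 = 0.45 points. Late vaccinees may respond more readily than people who would never vaccinate, so this too is an assumption.

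**The case against.** The strongest reply is that the protocol has already answered. Its second reason, that most vaccinations will have occurred, applies to both arms and limits how many can be displaced. That stands, and it would be wrong to say that the protocol argues only from the SMS arm. But it is not quantified, and against a 1-point target a few per cent of late vaccinees is enough to matter.

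A reader might infer from Table 1 that the plan defines coverage over a September-to-May season and so contradicts its own outcome. The documents do not support this. Table 1 describes an earlier season as background, the objectives name no closing date, and the Outcomes section fixes 3 months explicitly.

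A reader might also infer that the cost-utility model is specified to count moved vaccinations as extra vaccinees. The article says only that the model rests on observed differences; how it handles timing is not described. Earlier vaccination may have value of its own, and a season-end difference would ignore it.

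The fractions of 25-50% moved have no anchor in the documents, and the lower anchor above gives at most 0.45 points. The Kaplan-Meier curves help somewhat, since a gap narrowing towards month 3 would hint at acceleration, but they stop at the same line.

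Finally, a sensitivity analysis could sit in an analysis plan that is not shown. Here, though, the protocol itself ends follow-up at 3 months and expects the data in the first quarter of 2026, so under the stated data plan a season-end analysis would not be possible.

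**Conclusion.** The point holds as a limited weakness, not as an error in the primary outcome. Three-month coverage is a legitimate, clearly defined endpoint. What is missing is any means of telling added vaccinations from those moved across the 3-month line, although the protocol expects acceleration.

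The size cannot be established from the documents. With 1-5% of vaccinees late and 25-50% of those moved, it is 0.15 to 1.5 points in the general population; with 2.5-15% moved, it is 0.015 to 0.45. Against a 1-point target, much of that range would affect the interpretation. A reader might extend the concern to every primary comparison, but the figures do not bear that out: it is minor for Poland and negligible for Ukraine. It belongs chiefly to objective 1 and to the cost-utility model.

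**What to change.** - Keep 3-month coverage as the primary outcome, with the planned numbers unchanged.
- Extend the SYSVAK extract to season end, for example end of May 2026.
- Pre-specify the season-end coverage difference by arm as a secondary or sensitivity analysis, chiefly for objective 1, and state in advance how deaths and emigrations after month 3 are treated.
- Run the cost-utility model with the season-end difference as a scenario, or model vaccination timing explicitly so that any value of earlier protection is kept.
- State that a 3-month gain not kept at season end will be reported as earlier vaccination.

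The cost is one later or second registry extraction. Follow-up is passive and notification to SYSVAK is obligatory, and the data behind Table 1 were extracted on 31 May 2024, so this is feasible. The season-end data would arrive in about June 2026 instead of the first quarter, still ahead of publication in the fourth quarter. If late uptake proves trivial, the analysis will confirm the 3-month result.
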